This randomised controlled trial will determine whether wearing textured shoe insoles for 12-weeks can improve gait when walking over even and uneven surfaces in pwMS. The primary aim of this study is to explore whether prolonged wear of textured insoles alters ML base of support (as a measure of walking stability) from baseline assessment 2 to the post-intervention assessment. Secondary aims are to explore whether prolonged wear of textured insoles alters other spatiotemporal gait parameters including stride length, stride time variability, double-limb support time and gait velocity, gait kinematics (specifically lower limb joint and trunk movement), and changes in the perception of foot sensation or proprioception, as underlying mechanisms associated with improvements in spatiotemporal gait parameters.

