### Sample size

Sample size has been calculated for the primary outcome measure, ML base of support during even surface walking, based on our pilot data [20]. Our preliminary study reported mean (SD) readings at baseline for base of support of 13.78 (5.11) cm and a significant mean change of –1.66 cm (*P* = 0.02) at 2-weeks post intervention. With a power of 80 %, and alpha level of 0.05, a calculation for two related groups indicated that 76 participants were required in each group. In our pilot study, we recruited 46 pwMS, with no loss to follow-up across two visits (although completion of all test procedures was limited by fatigue in some participants). As this randomised controlled trial involves a longer intervention period, we will allow for a 15 % attrition rate. An 85 % retention rate over a 16-week period (baseline assessments at week 0 and week 4, intervention 12-weeks, post-intervention assessment at week 16) is appropriate based on previous MS intervention studies. Three randomised controlled trials with 12-week intervention periods conducted in pwMS, report retention rates of 82 % [27], 88 % [11], and 90 % [28]. Therefore, 88 participants per group will be recruited, giving a total of 176 participants.

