### Data analysis

All analyses will be conducted in a blinded manner, on an intention-to-treat basis, with the alpha set to 0.05. We will explore frequency distributions, percentages and calculate means and standard deviations for the outcome measures. Differences between intervention and control groups in spatiotemporal gait variables, gait kinematics, foot sensation or proprioception, over the intervention period, will be explored using General Linear Models (repeated measures analysis of variance, ANCOVA), in a two group (smooth control insole; textured insole) by three phase (baseline assessment 1, baseline assessment 2, post-intervention) model. We will adjust for potential confounding variables (e.g. age, sex, disease duration) by using these as covariates. Non-parametric tests will be used where data is not normally distributed or violates the assumption of sphericity. Multiple regression modelling will be used to determine any relationships between foot sensation, proprioception and measures of gait performance. Data will be analysed using SPSS version 22 (SPSS Inc., Chicago, IL 60606, USA).

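### Data analysis: failed sphericity is made a trigger for non-parametric tests, so a preliminary test on the outcome data can replace the covariate-adjusted primary comparison

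*Protocol article*

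**What the plan says.** The Data analysis section compares the arms with general linear models "in a two group (smooth control insole; textured insole) by three phase (baseline assessment 1, baseline assessment 2, post-intervention) model". It adds: "We will adjust for potential confounding variables (e.g. age, sex, disease duration) by using these as covariates". The next sentence sets the fallback: "Non-parametric tests will be used where data is not normally distributed or violates the assumption of sphericity". The article names neither a criterion for failure nor a replacement test.

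The primary aim, at the end of the Background, is narrower than the three-phase model. It asks whether prolonged wear "alters ML base of support (as a measure of walking stability) from baseline assessment 2 to the post-intervention assessment". The Sample size section gives the visit times ("baseline assessments at week 0 and week 4, intervention 12-weeks, post-intervention assessment at week 16"), so the gaps are 4 and 12 weeks.

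**The concern.** Sphericity is a condition on the covariance of the differences between phases. It matters for a within-subject F test with more than one degree of freedom. When it fails, the usual remedies are an epsilon correction to the degrees of freedom or a model with unstructured covariance. A contrast between two visits has one degree of freedom and its own error term, so sphericity does not enter. As written, failure of an assumption irrelevant to the primary question can change the primary analysis.

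The fallback also sits badly with the adjustment promised one sentence before it. The standard rank tests carry no covariates:

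- Friedman's test compares phases and has no between-group factor.
- Mann-Whitney on post values ignores baseline.
- Mann-Whitney on change uses baseline 2 but drops baseline 1 and the covariates.

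At stake are a primary test chosen by the trial's own outcome data and the loss of a covariate-adjusted difference in cm. The Primary outcome measures section judges the effect in cm, against a pilot reduction of 1.7 cm and a gap of about 2 cm from healthy controls.

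**Working it through.** **Inputs from the article (Sample size).** Baseline "base of support of 13.78 (5.11) cm"; "significant mean change of –1.66 cm"; "With a power of 80 %, and alpha level of 0.05" (two-sided assumed); 76 per group before attrition, so 152 evaluable.

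**Plan's own figure.** Paired formula: n = ((1.960 + 0.842) × 5.11 / 1.66)² = 74.4; the paired t solution is 76.3. Both are close to the stated 76, so SD 5.11 and effect 1.66 are the planning values used below.

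**Assumptions not in the article.** Correlations between visits and the shape of the distribution are unknown, so both were varied. The trigger was taken as Mauchly's test, or Shapiro-Wilk on within-group residuals at any visit, significant at 0.05. The 1.66 cm was placed between arms at the post visit only.

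**How large a departure from sphericity is in question.** Example with correlations 0.80 (baseline 1–baseline 2) and 0.70 (each baseline–post), unit variances, orthonormal contrasts:

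- Baseline 1 minus baseline 2: variance 1 − 0.80 = 0.200.
- Mean baseline minus post: variance (1.5 + 0.4 − 1.4)/1.5 = 0.333; covariance with the first is 0.
- Epsilon = (0.200 + 0.333)² / [2 × (0.200² + 0.333²)] = 0.284/0.302 = 0.94.

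This is a small departure, yet Mauchly's test rejects in 79% of simulated trials.

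**Simulation.** 1,500 trials per row, 76 per group, so the Monte Carlo standard error is about 1 point. GLM is the planned group-by-phase F test, without covariates or epsilon correction. ANCOVA is on baseline 2.

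| Correlations B1–B2 / B1–post / B2–post | Epsilon | Rule fires % | GLM % | Rank test on change % | Rank test on post % | ANCOVA % |
|---|---|---|---|---|---|---|
| 0.70/0.70/0.70 | 1.00 | 16.7 | 77.5 | 70.1 | 49.1 | 79.9 |
| 0.80/0.75/0.75 | 0.98 | 41.1 | 85.1 | 78.8 | 48.6 | 86.1 |
| same, post SD +10% | 0.96 | 68.5 | 81.9 | 75.5 | 42.1 | 79.6 |
| 0.60/0.50/0.50 | 0.98 | 41.9 | 55.9 | 50.4 | 50.7 | 64.3 |
| 0.60/0.50/0.60 | 0.98 | 46.6 | 58.1 | 56.6 | 49.9 | 69.7 |
| 0.70/0.60/0.60 | 0.97 | 57.1 | 65.1 | 57.1 | 51.1 | 72.0 |
| 0.80/0.70/0.75 | 0.95 | 73.3 | 82.3 | 79.3 | 49.4 | 85.7 |
| 0.80/0.70/0.70 | 0.94 | 81.9 | 78.9 | 70.7 | 49.0 | 80.1 |
| 0.85/0.70/0.75 | 0.88 | 99.7 | 83.2 | 79.9 | 50.5 | 85.1 |
| 0.85/0.70/0.70 | 0.86 | 99.9 | 79.4 | 71.3 | 48.5 | 79.3 |
| 0.90/0.80/0.80 | 0.86 | 99.9 | 92.7 | 87.3 | 51.1 | 91.4 |
| 0.90/0.75/0.80 | 0.81 | 100 | 87.3 | 84.7 | 48.0 | 89.8 |
| Lognormal, CV 0.37, 0.70/0.70/0.70 | – | 100 | 74.7 | 78.5 | 60.3 | 80.3 |
| Lognormal, CV 0.37, 0.80/0.70/0.70 | – | 100 | 74.9 | 76.7 | 61.4 | 79.1 |

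CV 0.37 is 5.11/13.78. Lognormal correlations are on the log scale. At CV 0.20 (SD 0.20 × 13.78 = 2.76 cm) the rule fired in 95% to 99% of trials, but power was 96% or more for every test, so those rows say nothing about loss.

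**Hand checks.** Unadjusted post comparison: SE = 5.11 × √(2/76) = 0.829; 1.66/0.829 − 1.960 = 0.04; power 52%, in line with about 49% for ranks. ANCOVA at correlation 0.70: SE = 0.829 × √(1 − 0.49) = 0.592; 1.66/0.592 − 1.960 = 0.84; power 80%, as simulated.

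**Loss against the planned model (GLM minus rank test on change).** Over the twelve normal rows it runs from 1.5 to 8.2 points, and ten of the twelve lie between 3.0 and 8.2. In the two lognormal CV 0.37 rows it is −3.8 and −1.8, that is, no loss.

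**The case against.** Four points can be made for the plan.

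1. *The rule may not fire.* A reader might infer from the unequal visit spacing that the switch would usually happen. The article does not support that: it gives no correlations, no distribution shape and no criterion. With normal data and equal correlations the rule fires in about one trial in six. What can be said is that it may well be triggered.
2. *The replacement test is not named.* A reader might infer that baseline or phase would be ignored. The article does not say so; ranking change scores uses baseline 2, and a condensed article may leave the choice of test to the full plan. This is granted, and no finding is made of the missing name. The point rests on the stated trigger and on the fact that the common rank tests carry no covariates.
3. *The power loss is modest.* A reader might infer that most of the precision goes. Against the model actually planned, ranking change scores loses single-digit points with normal data and nothing with skewed data. Setting it against an ANCOVA on both baselines (86% with all correlations 0.70) would overstate the cost, because the article does not plan that analysis. Only a post-only rank test is severely weaker.
4. *Rank methods suit some outcomes.* The sentence covers all outcomes, and monofilament thresholds and two-point discrimination are stepped or bounded. This stands, so deleting rank methods throughout would go too far.

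None of the four defends sphericity as a reason to leave the model, or a preliminary test as the selector of the primary analysis. A rank-based shift estimate could be given in cm, but it would not be covariate-adjusted.

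**Conclusion.** The point holds in this form: sphericity is wrongly made a trigger for rank tests, and the switch may replace the adjusted primary comparison by an unspecified, probably unadjusted test chosen by the outcome data. That conclusion needs no assumption about correlations or skew.

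Its size does need them. Across the assumed scenarios the rule fires in 17% to 100% of trials, although epsilon is only 0.81 to 1.00. With normal data, ranking change scores costs about 3 to 8 points against the planned GLM in most scenarios (78% to 70% with all correlations 0.70; 83% to 80% at 0.85/0.70/0.75). Ranking post values alone leaves 42% to 51%. With lognormal data at CV 0.37, ranking change scores loses nothing against the GLM, and what is lost is the adjusted estimate in cm.

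Two limits apply. The simulated models contain no age, sex or disease-duration covariates, so the cost of dropping these is not measured. The GLM figures use an uncorrected F test, which slightly favours the GLM where epsilon is below 1. The effect of the two-stage procedure on type I error was not assessed.

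**What to change.** Reword the fallback sentence in Data analysis:

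- Remove sphericity as a reason for non-parametric tests. For any three-phase test, use a Greenhouse-Geisser correction or a mixed model with unstructured covariance.
- For base of support and the other continuous gait outcomes, keep the covariate-adjusted group comparison from baseline 2 to post-intervention whatever preliminary tests show. If residuals (rather than raw data) are skewed, report robust or bootstrap 95% confidence intervals. Use rank methods as sensitivity analyses.
- For stepped or bounded sensory scales, rank-based analysis may stay, provided it is named in advance for each scale and not selected by a preliminary test.

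The cost is a few sentences of analysis wording. No change to visits, data collection or sample size is needed. The change should be made before unblinded outcome data are seen.

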## Discussion

Gait impairment is one of the most disabling and debilitating complaints reported by pwMS [5]. Deteriorating mobility observed in the early stages of disease [6–8] not only increases the risk of falling [1, 2], but frequently culminates in a complete loss of walking ability in the advanced stages [58]. The associated personal and societal burdens can have devastating implications for the individual, their families and national health services. Physical rehabilitation strategies reported to improve gait in pwMS commonly involve short-term multi-component exercise programs [9–13]. Maintenance of walking stability is attributed to optimal sensorimotor function; however, therapeutic management of gait impairments in pwMS largely focuses on addressing motor problems and poor aerobic capacity, and to a lesser extent sensory training, which is commonly addressed purely by way of balance tasks under a variety of sensory conditions. Interventions targeting sensory impairments at a more local level, including foot sensation and lower limb proprioception, are not frequently incorporated. This is a crucial area to address, as loss of foot sensation and impaired lower limb proprioception are strongly associated with standing balance and gait performance in pwMS [15, 19]. Therefore, the effectiveness of current strategies for managing mobility in pwMS could be further enhanced by using a wider range of treatment techniques.

Providing enhanced sensory input to the plantar surface of the feet has recently been considered a potential mechanism through which footwear interventions may improve gait [21, 22, 24, 59–63] by way of altering sensorimotor function. Underlying physiological mechanisms by which a textured insole may initiate changes in gait are suggested to include the provision of sufficient tactile stimulation to alter the rate of discharge from mechanoreceptors or firing patterns of populations of sensory afferents located in the feet. Textured shoe insoles appear to have the capacity to alter gait patterns, potentially improving gait stability in ageing, neurodegenerative and neuromuscular disease groups with known balance impairments. To date, exploratory studies report that wearing shoe insoles deigned to enhance plantar sensation can significantly increase single-limb support time [24], increase stride length and reduce double-limb support time [32] during walking in people with Parkinson’s disease. Similar conclusions are emerging for pwMS, with exploratory work observing beneficial alterations in spatiotemporal gait parameters [20], gait kinetics and kinematics [21].

This randomised controlled trial will use fundamental knowledge of sensory and motor function in MS to develop novel ways to improve gait by way of enhancing sensory information at the soles of the feet. Preliminary work in this clinical population [20] provides strong evidence of improvements in gait patterns when textured insoles were worn (as a single intervention) for 2 weeks. It is possible that the benefits of wearing textured insoles may accrue, and that additional benefits may be observed, over a longer period of time. Findings from this trial could have implications on the management of gait impairment in pwMS. The benefit for pwMS (and their families) is that this study may lead to the development of a new, evidence-based footwear intervention which is inexpensive, non-invasive, promotes self-management by the user, and has the capacity to enhance mobility and independent living. Furthermore, addressing problems with mobility, and subsequently quality of life, could have a major economic impact through improvements in productivity or reducing working days lost. The benefit for healthcare professionals is that this study may generate vital evidence to inform the development of more effective, multi-faceted and multi-disciplinary rehabilitation programmes, which are tailored to address a greater range of MS-specific impairments that contribute to deteriorating gait. This could have major implications on current clinical guidelines and policy relating to physical rehabilitation strategies for pwMS.

### Trial status

Ongoing.

## Abbreviations

EVA: Ethyl vinyl acetate
ML: Mediolateral
MS: Multiple sclerosis
pwMS: People with multiple sclerosis
